### Aims of the Study

The aims of this study are 3-fold: (1) develop an algorithm of predictability based on biofeedback, (2) address feasibility and acceptability of a preprocedural immersive VR (IVR) game preparation before an MRI procedure for children’s anxiety (field test phase), and (3) examine the efficacy of a preprocedural IVR game preparation compared with usual care for the management of procedural anxiety in children undergoing an MRI examination (by conducting a randomized controlled trial [RCT]).

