### Inclusion Criteria

Children and their parents will be invited to participate in the study if they meet the following inclusion criteria: (1) aged 7 to 17 years; (2) required to undergo an MRI procedure; and (3) accompanied by a consenting parent or legal guardian who can understand, read, and write either French or English.

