### Measures and Outcomes

#### Sociodemographic and Clinical Questionnaire

Demographic and clinical characteristics will be assessed with parent reports filled out by the research nurse using the case report form and will include data on age, sex, ethnicity, reason for MRI imaging study, and history of imaging studies, including MRI, computed axial tomography scans, and x-ray examinations. Data such as name, dosage, and time of administration of anxiolytics taken 24 hours before the MRI examination will be collected. The questionnaire will also include a section describing the context of the procedure including adherence to the intervention, total procedure time, use of other nonpharmacological interventions, and the occurrence of side effects.

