##### Primary Outcome Analyses

An analysis of covariance (ANCOVA) adjusted for age, sex, baseline (T0) Trait anxiety score measurement, and baseline State anxiety score measurement will be used to assess the mean difference in State anxiety scores on the STAIC-State between the experimental and the control groups at T2. Analyses will be carried out according to the intention-to-treat principle, with a significance level (Cronbach α) of .05.

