##### Secondary Outcome Analyses

An ANCOVA adjusted for age, sex, and baseline anxiety score measurement will be used to assess the mean difference in anxiety scores on the CFS, between the experimental and the control groups at T2. To assess the mean difference in the sense of presence in VR and engagement into the game (GRS), between the experimental and the control groups at T1, an ANCOVA adjusted for age and sex will also be conducted. We will use a linear mixed model to estimate the effect of the treatment on the changes in heart rate over all assessment time points. This analysis will be adjusted for age, sex, and baseline heart rate. Differences between arms for levels of satisfaction of parents, children, and health care professionals (T2) as well as the overall procedure time will be assessed using (2-tailed) *t* tests or nonparametric Mann-Whitney *U* tests if data are nonnormal. A chi-square test or Fisher exact test will be conducted to compare dichotomous variables including the occurrence of side effects, the number of rescheduled MRI examinations, and the use of sedation in each group.

Adverse events and serious adverse events (if any) will be reported using the Medical Dictionary for Regulatory Activities terminology, and their proportions will be compared between the groups.

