To help develop the predictability algorithm, the head deviations and other physiological data will be analyzed. An algorithm based on those deviations will be developed prospectively as the study progresses to evaluate the success of the MRI procedure in the intervention context and offer useful predictability inputs in preparation for the real MRI examination. No existing algorithms specific to the study were found. The physiological data will also help create a time sequence that could be matched with the information that will be extracted from the intervention. At the end of the session, it will be possible to see if, for example, a movement of the patient is generally triggered by an increase in stress as captured by the sensors. The result of the examination will then be compared with the data obtained during the intervention. The team will attempt to determine which variables correlate with the real-life outcome. Our hypothesis is that a patient who can follow the instructions well without any signs of anxiety captured by physiological parameters will have better results in the MRI procedure than a patient who has difficulty following the instructions or who shows signs of anxiety expressed through their physiological parameters.

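### The predictability algorithm is described as a correlation of intervention-phase signals with the MRI result across ages 7 to 17, with no age or baseline-anxiety benchmark to show what biofeedback adds

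*Protocol article*

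**What the plan says.** Aims of the Study in the protocol article lists as aim 1 to "develop an algorithm of predictability based on biofeedback". The method is in the last paragraph of Secondary Outcome Analyses:

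- Inputs: "the head deviations and other physiological data will be analyzed".
- Basis: "An algorithm based on those deviations will be developed prospectively as the study progresses to evaluate the success of the MRI procedure".
- Selection: the examination result is compared with the data obtained during the intervention, and "The team will attempt to determine which variables correlate with the real-life outcome".

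The eligible population is "aged 7 to 17 years; (2) required to undergo an MRI procedure". The neighbouring analyses treat age differently. The primary ANCOVA is "adjusted for age, sex, baseline (T0) Trait anxiety score measurement, and baseline State anxiety score measurement". For the heart-rate mixed model, "This analysis will be adjusted for age, sex, and baseline heart rate". The Children's Fear Scale and Graphic Rating Scale ANCOVAs also adjust for age and sex.

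What a benchmark needs is already collected. The case report form "will include data on age, sex, ethnicity, reason for MRI imaging study, and history of imaging studies", the full STAIC-F is completed at T0, and the research nurse notes heart rate at T0.

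**The concern.** The comparison described is between children: each child has one examination result, and signals from the session are related to it. If older children tend to have slower heart rates, move less and complete the scan more often, those signals will correlate with success even if they say nothing beyond the child's age. A plain correlation cannot tell that case from a real biofeedback signal.

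This bears on what the article intends to conclude. The abstract's Conclusions and the Clinical Trial section of the Discussion credit biofeedback with predicting which children respond. The latter also expects the algorithm to point to modifiable participant factors, and age is not modifiable. At stake is whether a sensor device is credited with information that a date of birth already supplies. The primary efficacy comparison is not affected.

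**Working it through.** **The plan's own figure.** The only calculated figure is the trial sample size; none is given for the algorithm. With difference 5, SD 7.47 and two-sided 5%, the noncentral t gives power 79.97% at 36 per group and 81.07% at 37, so 37 reproduces. Then 37 / (1 − 0.24) = 48.7, rounded up to 49 per group, 98 in total. This is not in dispute. It matters here because head deviation and the sensor signals are recorded during the simulation. By inference about 49 children contribute, or about 37 after attrition, plus possibly the 10 in the field test.

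**Mechanism.** If signal and outcome are linked only through age, then r(signal, outcome) = r(signal, age) × r(outcome, age). With both age correlations at 0.5, the unadjusted correlation is 0.5 × 0.5 = 0.25, although the partial correlation given age is zero.

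**Check 1: continuous outcome, assumed age correlations** (20,000 runs each, two-sided 5%).

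| r(signal, age), r(outcome, age) | Unadjusted, n = 37 | Unadjusted, n = 49 | Age-adjusted |
|---|---|---|---|
| 0.3, 0.3 | 8% | 9% | about 5% |
| 0.5, 0.3 | 15% | 18% | about 5% |
| 0.5, 0.5 | 32% | 42% | about 5% |
| 0.7, 0.5 | 58% | 71% | about 5% |
| 0.7, 0.7 | 89% | 95% | about 5% |

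**Check 2: heart rate and a yes/no scan result.** All inputs below except n are assumptions.

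- Age is uniform from 7 up to the 18th birthday, so its SD is 11/√12 = 3.18 years.
- Heart rate = 90 − b(age − 12.5) + error, with error SD 11 bpm.
- logit(success) = logit(p) + ln(OR)(age − 12.5).
- Low, middle and high settings: b = 1, 2, 3 bpm per year with OR = 1.2, 1.35, 1.5 per year.

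In the middle setting the correlation of heart rate with age is 2 × 3.18 / √(6.35² + 11²) = −0.50 after taking the sign. Percentage of trials with a significant unadjusted correlation (ranges are across repeated runs):

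| Success p at age 12.5, n | Low | Middle | High |
|---|---|---|---|
| 75%, n = 49 | 7–8% | 26–27% | 60–62% |
| 75%, n = 37 | 7% | 20% | 48–49% |
| 90%, n = 49 | 5–6% | 16% | 38–41% |
| 90%, n = 37 | 5–6% | 13% | 29–31% |

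With age in the model the rate is about 4% to 6% throughout. The mean AUC of heart rate alone at p = 75% runs from about 0.54 to 0.70.

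**Check 3: can an in-sample gain serve as the test?** No. Adding five pure-noise signals to an age-plus-anxiety logistic model (n = 49, p = 75%, assumed) raised the apparent AUC in 98% of simulated trials, by about 0.07 on average. Unsuccessful scans are few: about 13 to 15 of 49 at p = 75%, and about 6 to 8 at p = 90%.

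**The case against.** The strongest reply is that the omission is inferred from silence. The paragraph names no model and no closed list of predictors, the phrase about which variables correlate is open, and a journal article may leave model specification to a fuller document. This stands in part. A reader might infer that the plan excludes age and uses raw signals, but the text says neither, and T0 heart rate is available as a reference. What remains is that the article does state a method, namely data from the intervention compared with the result by correlation, and that method contains no age or anxiety comparator.

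Second, the paragraph also describes a time sequence within the child, asking whether a movement follows a rise in stress. Age is constant within a session and cannot confound that. This is right, but the later step of relating session data to the examination result is between children, and there age can.

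Third, covariates in the between-arm models mainly serve precision and do not bind a prediction exercise. Also, a stand-in for age still predicts. Both are correct. A reader might infer that such an algorithm would be wrong or useless, and the documents do not support that. Only the attribution to biofeedback, or a claim of information beyond age, would fail.

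Fourth, the magnitude is assumed. Eligibility is limited to children judged not to need sedation, so a high success rate and a weak link between age and success are plausible, and then the excess is small. Only heart rate was simulated on the yes/no result, so nothing here shows that every signal would correlate with success. This stands, and it is why a range is given.

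Finally, the work is worded as exploratory. That limits the severity, but the abstract and discussion do not keep the same caution.

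**Conclusion.** The point holds as a weakness in the described method. Followed as written, it cannot separate a biofeedback signal from a stand-in for age across ages 7 to 17, while the article's neighbouring heart-rate and anxiety models do account for age. The size cannot be derived from the documents. Under the heart-rate assumptions shown, about 5% to 62% of trials would give a significant unadjusted correlation for a signal with no information beyond age, against about 5% with age adjustment. At the weak end of the assumptions there is almost no problem. The finding does not show that age was deliberately left out, that the algorithm would fail to predict, or that the treatment comparison is biased. It is worth correcting because it concerns one of three stated aims and the conclusion drawn from it.

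**What to change.** Amend the algorithm paragraph in Secondary Outcome Analyses as follows:

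1. Fit a benchmark model for the MRI result with age and T0 State anxiety only. Two variables are enough, given how few scans are likely to be unsuccessful.
2. Add a small prespecified set of biofeedback variables, with heart rate as change from T0.
3. Report the gain in discrimination over the benchmark, cross-validated or bootstrap optimism-corrected, with its confidence interval.
4. Limit the conclusion to an exploratory statement on added value over age and baseline anxiety. Do not credit biofeedback on the strength of an unadjusted correlation or an in-sample gain. Bring the abstract and discussion wording into line.

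The cost is analysis wording and modest extra computing; no new data are needed. The downside is that the gain will be imprecise with few unsuccessful scans, and the biofeedback result may look less impressive.

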### Study Proceedings (Clinical Validation Phases)

Participants will be identified through the radiology information system as having an appointment for an upcoming MRI procedure. Either the physician prescribing the MRI examination or the radiologist will have indicated certain patients as not needing sedation during the MRI examination and thus identified as eligible for this study. The research nurse will be notified by the radiology technologist and will contact the parents for recruitment a few days before the procedure. On the day of the appointment, parents will be approached to sign the consent if they still agree to the study. The child’s assent will also be obtained on the same day. Participants are informed of their assignment to either the preprocedural IVR game preparation or usual care group after randomization. Before initiation of the procedure, the research nurse will explain the intervention to the patient and install the IVR game preparation and start the video game program. Baseline measurements of anxiety will be taken before the interventions in the waiting room (T0).

The research nurse will log in 10 minutes before the IVR video game preparation or usual care interventions to obtain the group allocation of the participant if they meet all eligibility criteria. Given the nature of the interventions, the participants and personnel cannot be blinded to the interventions. However, to minimize observer bias given the subjective measures of outcomes, parents and children will only be informed to which group they are assigned 10 minutes before the intervention. Data will be collected on paper forms and then the information will be transferred into REDCap (Research Electronic Data Capture; Vanderbilt University) by a research nurse. Data on game completion by the child will be recorded but no data will be collected on specific game inputs. Furthermore, although a separate screen allows research staff and parents to watch the child’s perspective, none of it will be recorded. The paper copies of the data forms will be kept locked. The data will be reviewed by a data manager to check for possible errors. The informed consent, assent, and baseline data collection will require approximately 10 minutes. After randomization, the IVR game preparation intervention will last for 15 to 20 minutes. Postintervention data collection will require approximately 10 minutes. In total, the duration of the intervention period, from recruitment to discharge, will be 30 to 40 minutes for each participant. Time has been allocated to the clinical workflow to allow for the research nurse to clean the VR technology before the arrival of each new patient.

Data collection forms of the participants will be stored under a double lock at one of the principal investigators’ office at the research center and will be kept for 7 years after the end of the trial. As this is an open-label clinical trial and no prior data suggest that any of the 2 interventions are associated with side effects, a data monitoring committee is not required. However, the occurrence of any side effects will be reported to the ethics committee. VR technology such as a head-mounted display (eg, Pico Neo II VR Helmet) has the potential to cause motion sickness, including discomfort, disorientation, and nausea. To overcome this issue, the development team specialized in immersive technology had previously developed a game that fully maximizes the experience of immersion and the sense of being in a virtual environment while minimizing motion sickness. During a previous pilot study using this VR game, no participant reported motion sickness symptoms while using IVR [43].

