### Objectives

The primary research question concerns whether preprocedural interaction-enabled IVR game preparation will decrease MRI examination–related procedural anxiety for children undergoing an MRI procedure. The secondary objectives of the scientific clinical validation phases are as follows:

To determine whether preprocedural IVR game preparation is a feasible and acceptable nonpharmacological method to decrease MRI examination–related procedural anxiety.To determine whether children experiencing preprocedural IVR game preparation will have a slower heart rate before and during the MRI procedure than children not exposed to the IVR game preparation.To determine whether children experiencing preprocedural IVR game preparation will require lower need for sedation than children not exposed to the IVR game preparation before an MRI examination.To determine whether children experiencing preprocedural IVR game preparation will require rescheduling of the examination less often than children not exposed to the IVR game preparation before an MRI examination.To evaluate the occurrence of side effects with preprocedural IVR game preparation in comparison with children not exposed to the IVR game preparation before an MRI examination.To compare satisfaction levels of health care professionals between preprocedural IVR game preparation and usual care groups.To compare satisfaction levels of children and parents between preprocedural IVR game preparation and usual care groups.To compare overall procedure time required for an MRI examination between preprocedural IVR game preparation and usual care groups.To develop a predictability algorithm that will help identify which children will have better results in the MRI procedure after the IVR game preparation.

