#### Secondary Outcomes

The secondary outcomes were (1) mean difference in the sense of presence and engagement (immersion) into the VR game between groups (T1), (2) the presence of head deviation during the intervention, (3) changes in physiological signs through biofeedback during the intervention, (4) satisfaction levels of parent (T2), (5) satisfaction levels of children (T2), (6) satisfaction levels of health care professionals (T2), (7) occurrence of side effects, (8) mean difference in total procedure time and frequency of rescheduling MRI examinations between groups, and (9) mean difference in Trait anxiety levels between groups.

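### The protocol's claim that personnel cannot be blinded is too broad: nothing in it requires whoever judges image adequacy after the scan to know the arm, and rescheduling is compared between arms

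*Protocol article*

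**What the plan says.** The protocol article, under Study Proceedings (Clinical Validation Phases), rules out masking for everyone involved: "Given the nature of the interventions, the participants and personnel cannot be blinded to the interventions". It then names observer bias as a worry, since outcomes are subjective, and offers one safeguard: "parents and children will only be informed to which group they are assigned 10 minutes before the intervention". The same section later calls the study open-label ("As this is an open-label clinical trial").

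Several between-arm comparisons may depend on decisions by staff:

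- Objectives: children given the game "will require rescheduling of the examination less often than children not exposed" to it, and they "will require lower need for sedation than children not exposed to the IVR game preparation".
- Secondary Outcomes, item 8: "mean difference in total procedure time and frequency of rescheduling MRI examinations between groups".
- Secondary Outcome Analyses: a chi-square or Fisher exact test of side effects, "the number of rescheduled MRI examinations, and the use of sedation in each group".

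Sedation is therefore an objective with a planned test, although the numbered list of secondary outcomes does not include it. The primary outcome is the child's own State anxiety score on the STAIC-F after the scan.

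**The concern.** The reason given for not masking is the nature of the interventions. That is sound for people who take part in the preparation or watch it. It says nothing about a person who sees only the images. By treating all personnel alike, the article rules out a safeguard that may be available for at least one role.

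The one safeguard it does adopt is aimed at families. It delays their knowledge of the allocation but does not touch what staff know when they judge a scan.

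What is at stake is the rescheduling comparison. If a reader who knows that a child had the game is more willing to accept a borderline scan, fewer repeats will be recorded in that arm even if the game changes nothing. The Discussion leans on fewer failed and repeated tests as an argument for adopting the game, so the comparison matters although it is secondary.

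**Working it through.** **Step 1. Which roles does the stated reason cover?**

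| Role | What the article says | Must know the arm? |
|---|---|---|
| Child and parent | Receive or watch the preparation | Yes |
| Research nurse | Obtains the allocation, installs and starts the game | Yes |
| Radiology technician | Gives the standard explanation in usual care | Probably |
| Whoever judges the images after the scan | No part in the preparation described | Nothing requires it |

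**Step 2. Is a between-arm outcome linked to image quality?** Yes, in part. The Background describes restless children moving, images that are not diagnostic, sometimes an early end to the procedure, and then a repeat. Rescheduling is an objective, a listed outcome and a planned test.

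**Step 3. The plan's own figures.** Sample and Setting gives 145 procedures prescribed and 193 carried out in 2020. The excess is 193 − 145 = 48, and 48/193 = 24.9%, as stated. The group size also reproduces: 37/(1 − 0.24) = 48.7, rounded up to 49 per arm. The 24.9% counts delays as well as repetitions, so it is only a rough guide to a repeat rate. I use 25%.

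**Step 4. Illustration.** Inputs: n = 49 per arm (from the plan), a true repeat rate of 25% in both arms (assumed), and a share w of needed repeats waived in the IVR arm only (assumed). The observed IVR rate is 0.25 × (1 − w). For every pair of counts (i in usual care, j in IVR), the probability is Bin(i; 49, 0.25) × Bin(j; 49, 0.25(1 − w)). I sum it over the pairs that favour IVR and are significant at the two-sided 5% level. Chi-square is uncorrected: z = (i − j)/49 ÷ √[p̄(1 − p̄) × 2/49] > 1.96, with p̄ = (i + j)/98.

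| w | Observed IVR rate | Chi-square | Fisher |
|---|---|---|---|
| 0 | 25% | 2.5% | 1.5% |
| 1 in 10 | 22.5% | 4.7% | 2.9% |
| 1 in 5 | 20% | 8.6% | 5.5% |
| 1 in 4 | 18.75% | 11.3% | 7.4% |

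With a 5% repeat rate and one in five waived (4% observed), the figures are 4.1% for chi-square and 0.6% for Fisher. The effect is therefore small if repeats prompted by image quality are rare.

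**Step 5. What masking an image reader can reach.** It reaches repeats ordered because the finished images are inadequate. It does not reach a scan stopped in the session, sedation given at the scanner, or total procedure time. Those depend on people who probably know the arm: the technician gives the usual care explanation, and the nurse notes heart rate during the scan.

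**The case against.** The strongest reply is that the article never says who decides on a repeat, a rescheduled scan or sedation. It does not say that the image reader works apart from the scanner. The Background also describes stops during the session, which would be decided on the spot. This stands, and it limits the point to judgements of image adequacy after the scan. It does not rescue the categorical sentence, whose stated reason still does not extend to that role.

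The waiver rates are not in the article, nor is anything about staff expectations. This also stands. The figures show a mechanism and do not estimate a bias. A reader might infer that the comparison is biased towards IVR; the article supports only that it could be.

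A reader might also infer that masking the radiologist would protect the sedation comparison, since "Either the physician prescribing the MRI examination or the radiologist will have indicated certain patients as not needing sedation". That sentence describes an eligibility step completed before consent and randomization, so knowledge of the arm cannot affect it. It does not show who decides on sedation later.

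Finally, a journal article may leave reading procedures to the full protocol, and the trial is openly described as open-label. The point here is not that a procedure is missing. It is that the article states that masking cannot be done, for a reason that does not apply to every role.

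**Conclusion.** The concern holds in a limited form. The no-blinding sentence claims more than its reason supports, and the only mitigation does nothing about staff. As a result, the rescheduling comparison is open to a bias that could be partly removed.

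Under an assumed 25% repeat rate with one in five repeats waived in the IVR arm, the chance of a false finding in favour of IVR goes from 2.5% to 8.6% with chi-square and from 1.5% to 5.5% with Fisher. Both the rate and the waiver are assumptions. So is the idea that the image reader's judgement leads to the repeat.

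Two stronger readings are not supported. One is that masking one reader would protect sedation or procedure time. The other is that the primary result is at risk from this source: it is the child's self-report, and masking the image reader leaves it unchanged. The planned 98 participants also stay as they are.

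**What to change.** 1. Limit the sentence to the child, the parent, the research nurse and staff who deliver or see the preparation.
2. Keep the allocation out of the imaging request and the radiology record.
3. Have the existing image reader classify each scan as diagnostic or needing a repeat without knowing the arm.
4. Record on the form who made each repeat, stop or sedation decision and whether that person knew the arm. This makes the remaining bias visible but does not remove it.
5. Report sedation, in-scan stops and procedure time as open to performance and detection bias.

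No criterion for repeating, stopping or sedating needs to change.

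The cost is low but not zero: protocol wording, one form field, control of access to the allocation, and a satisfaction questionnaire that a masked radiologist completes only after reporting or not at all. No additional reader is needed if the person who already reads each scan does this. The Design section allows changes between the field test and the RCT but none afterwards. The Results section reports no RCT participant recruited as of May 10, 2022, so the change was still possible on the article's own timetable.
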